##### **In healthy volunteer participants (CTL group):**

- T1 assessment will take place within 6 weeks of inclusion assessment
- T2 assessment will take place 6 months after T1

##### **For all study participants, the following assessments will be proposed at T1 and T2:**

- Actigraphy and sleep diary (for 2 weeks before each check-up)
- Questionnaires to be completed at home (sleep and quality of life):
  - o ISI
  - o PSQI
  - o Horne and Ostberg
  - o FACT-G (patients only)
  - o FACIT-F (patients only)
  - o MFI-20
  - o FACT-Cog
- Diurnal salivary cortisol and CAR (Cortisol Awakening Response) assays
- MRI (aMRI and fMRI at rest and activation with ANT task + post-MRI debriefing questionnaire)
- Spatial memory task
- Polysomnography
- Neuropsychological tests :
  - o MoCA (T1 only)
  - o HVLT
  - o Space Memory Subtest (MEM-III)
  - o Baddeley's double task
  - o N-Back
  - o d2-R
  - o TMT A and B
  - o Spelling fluency
  - o Stroop
- Questionnaires (quality of life) :
  - o KSS
  - o BDI-II
  - o BPI

- STAI - State
- STAI - Trait
- PCL-5 (patients only)
- PSS
- Modified dispositional brief-COPE (before cancer diagnosis) (patients only, T1 only)
- Dispositional COPE Brief
- PTGI
- IPAQ

-Assessment of vestibular function (video Head Impulse Test, vHIT)

#### 8.4.5 Balance sheet T3

**For all participants**, the following assessment will be carried out at the end of the GVS or SHAM period (2 weeks) after T2.

- Actigraphy and sleep diary (between T2 and T3)
- Questionnaires to be completed at home (sleep and quality of life):
  - ISI
  - PSQI
  - Horne and Ostberg
  - FACT-G (patients only)
  - FACIT-F (patients only)
  - MFI-20
  - FACT-Cog
- Dosing of diurnal salivary cortisol and CAR (Cortisol Awakening Response)
- Spatial memory task
- Polysomnography
- Neuropsychological tests :
  - HVLT
  - Space Memory Subtest (MEM-III)
  - Baddeley's double task
  - N-Back
  - d2-R
  - TMT A and B
  - Spelling fluency
  - Stroop
- Questionnaires (quality of life) :
  - KSS
  - BDI-II
  - BPI
  - STAI - State
  - STAI - Trait
  - PCL-5 (patients only)
  - PSS
  - Dispositional COPE Brief

- PTGI
- IPAQ

-Assessment of vestibular function (video Head Impulse Test, vHIT)

## 8.5 PREMATURE STUDY TERMINATION

The intervention will be interrupted at any time in the following circumstances:

- Intercurrent event not compatible with continuation of study
- Participant's decision (data already collected during research may be retained and used unless the subject objects)
- Lost participant
- Investigator's decision

## 8.6 METHODS OF CARRYING OUT PARTICIPANT EVALUATIONS

For T1 and T2, participants will be received in the early afternoon at GIP Cyceron (Caen) to perform MRI sequences in the presence of an investigating physician.

Further assessments will take place at the PFRS, located in the immediate vicinity of Cyceron.

At T3, participants will be received directly by the team at PFRS Caen to carry out all the assessments.

The spatial memory task, the cognitive tests battery and the questionnaire sessions will be carried out in a specially adapted room at UMR 1077, with a psychologist specialized in neuropsychology.

The polysomnography equipment will be installed and removed by two specialized sleep technicians in a dedicated room at UMR 1077.

The vHIT will be performed at times T1, T2 and T3 at the PFRS by a technician trained to perform this test. The results will be interpreted by a physician specializing in vestibular function and attached to the ICANSLEEP protocol.

The night time during which participants will wear the polysomnography equipment is not included in the above durations. For the night between the 2 half-days of assessment, participants can either go home or stay in a hotel, at their own expense. At each stage of the assessment, participants will be given part of the questionnaires (sleep and quality of life) to complete at home.

A total indemnity of 300 € will be given to each participant in return for the constraints and time invested during their participation in the study. In the event of premature exit from the study, compensation will be paid on a pro rata basis, i.e. €100 per evaluation time completed or not.

# 9 EVALUATION TOOLS

## 9.1 Quality and physiology of sleep and circadian rhythms

In addition to subjective measures (self-questionnaires), objective measures (actigraphy, PSG) will be used to collect the participants' sleep quantity and quality indices.

### 9.1.1 Self-assessment of sleep and circadian typology

Sleep questionnaires (ISI and PSQI) are to be completed at home between the two evaluation sessions, to provide information on subjective sleep parameters. The ISI focuses specifically on insomnia-related symptoms, while the PSQI measures participants' overall subjective sleep quality. The Horne and Ostberg questionnaire  provides information on circadian typology.

THE ISI  is a 7-item Likert scale assessing symptoms associated with insomnia. A score above 8 indicates the presence of a complaint associated with insomnia.

The PSQI  is a questionnaire evaluating 7 components associated with sleep (quality, duration, sleep onset latency, sleep efficiency, use of hypnotics, sleep alterations and impact on daytime functioning). The score ranges from 0 to 21, with a score of 5 or more considered to represent a complaint of poor sleep.

Horne and Ostberg's circadian typology questionnaire  includes 19 items to determine circadian typology (very much morning, moderately morning, neutral, moderately evening, very much evening) on the basis of a total score between 16 and 86.

All 3 questionnaires can be completed in 15 minutes.

### 9.1.2 Sleep/wake cycle test

To quantify periods of activity and rest, and thus the alternation of sleep/wake rhythms, an actigraph (a watch-sized accelerometer worn on the wrist) with a sleep diary will be provided to participants 2 weeks before each assessment time (T1, T2 and T3).

The main parameters derived from the analysis of actigraphy data are the amplitude and acrophase of the activity-rest rhythm.

### 9.1.3 Examination of nocturnal sleep

At each stage of the study, PSG sleep recording will be carried out at the participants' homes or hotels, using a portable device (Siesta, Compumedics). The equipment will be set up at the PFRS by our research team, and will take around 2 hours to set up. Recordings of brain activity (electroencephalography), eye movements, heart rate, respiratory rate and oxygen saturation will be made simultaneously throughout the night. Sleep scoring (i.e. characterizing the alternation of different sleep stages) will be carried out by a sleep technician. The technician's intervention will also detect any sleep apnea syndromes, and participants will be referred to a specialist if necessary. Participants will be asked not to drive while wearing the polysomnography equipment.

The main parameters derived from PSG analyses are the number of intra-sleep arousals and sleep efficiency (total sleep time/time spent in bed).

### 9.1.4 Physiological measurements related to circadian rhythms and stress response

Repeated saliva sampling will be carried out at each stage of the study (*Table 3*) to study changes in salivary cortisol levels, one of the markers of circadian rhythms, as well as certain stress-related responses (*Cortisol Awakening Response*).

**Table 3** Cortisol measurements according to evaluation times

|                                                     | T1 and T2 | T3 |
|-----------------------------------------------------|-----------|----|
| Before and after MRI                         | •         |    |
| CAR
- Waking up
- 30 min.
- 45 min. | •         | •  |
| Bedtime                                      | •         | •  |
| Before and after rest                        | •         | •  |
| Total measurements                           | 8         | 6  |

**Note.** CAR: Cortisol Awakening Response

Participants will be provided with Salivette® systems for saliva testing. This device involves inserting a cotton ball into the mouth and soaking it in saliva for 2-3 minutes, then returning it to the storage tube.

Participants will receive a description of the procedure to remind them of the instructions (no drinking, no eating, no smoking, no brushing teeth in the 30 minutes prior to collection) and a table to enter the time of collection. Morning samples will be collected at the participant's home or hotel, and placed in an insulated bag to be stored at 4°C before being transported to the laboratory in the morning. The remaining samples will be collected in our research unit. All salivary samples will be centralized and stored at -80°C at the Centre François Baclesse, in a secure environment with optimum traceability. These samples will be sent to [name]'s team in Rouen (Inserm, U1239, Dir: [name]) for salivary cortisol determination. Parameters that may influence salivary cortisol levels will also be collected (age, body mass index, smoking habits, contraceptive methods, socio-educational status).

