## 6 RESEARCH HYPOTHESIS AND EXPECTED RESULTS

##### Axis 1:

- 1)
  - a) Sleep and circadian rhythms would be altered in patients before chemotherapy compared with cancer-free subjects. Chemotherapy would exacerbate these effects compared with the no-chemotherapy group
    - For sleep, more awakenings lasting more than a minute and poorer sleep quality are expected.

- For circadian rhythms, the sleep/wake and cortisol rhythms are expected to be less ample.
- b) Altered rhythms have deleterious effects on sleep quality**
- 2)** Cognitive abilities would be more impaired after than before chemotherapy, whereas no decline is expected in patients not treated with chemotherapy and in healthy subjects. More specifically, this decline is expected to affect:
    - Spatial and episodic memory
    - Working memory
    - Executive and attentional functions
    - Functional connectivity during the ANT (Attentional Network Test) task, particularly within the orientation and cognitive control networks
  - 3)** After chemotherapy, the cortical structure should be altered, particularly in the regions involved in the above-mentioned cognitive abilities (i.e., hippocampus, frontal regions, cerebellum) compared to before chemotherapy, and compared to patients not treated with chemotherapy and healthy subjects.
  - 4)** For both groups of patients, the dynamics of functional connectivity at rest prior to chemotherapy should be altered, with greater ruminations than in the healthy group.
  - 5) a)** Sleep disturbances (independently of the effects of anxiety and depression) are thought to be linked to cognitive abilities and their neuro-anatomical correlates, specifically:
    - Episodic and spatial memory performance
    - White matter structure and functional connectivity
  - b)** Sleep disturbances are also associated with hyperactivity of physiological stress systems
  - c)** Sleep disturbances are associated with a lower quality of life

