#### **8.4.2 Study evaluations**

A table summarizing the investigations requested and a diagram showing the different stages in the evaluation of participants are included at the beginning of the document (*Figure 1*).

The first evaluation will be carried out within one month of inclusion and before the start of chemotherapy (CHI group) or radiotherapy (NCH group), depending on the availability of participants.

Throughout the evaluation sessions, participants will be accompanied by the UMR 1077 team, comprising a neuropsychologist, a sleep technician and a PhD student.

Prior to the assessment sessions, actigraphy data will be collected from participants 2 weeks before each assessment session (T1, T2 and T3). For this purpose, an actigraph and a sleep diary with explanations on how to use them will be provided to participants either *in person*, or remotely (actigraph and sleep diary sent by post and videoconference).

The assessments proposed to the participants during the different study phases (T1, T2 and T3) are presented in the following figures (*Figure 2* and *Figure 3*). Each evaluation sequence will be carried out over 2 half-days (afternoon and morning), separated by a night's sleep to allow polysomnography examination.

[figure not shown]

**Figure 2.** Assessments offered to participants at T1 and T2

**Note.** Actigraphy will be provided 2 weeks before T1, idem at T2; At T1, a preliminary interview will take place at the reception of the participants (approximately 30 min, in addition to the MRI instructions); At T1, a period of familiarization with the galvanic vestibular stimulation equipment will take place before the MRI examination (20 min); PSG:

[figure not shown]

**Figure 3.** Assessments offered to participants at T3

**Note.** Actigraphy will be provided 2 weeks before T3; PSG: Polysomnography

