|                                                                                                                                             | Spelling fluency 

 
• P (T1)
 
• R (T2)
 
• V (T3)
 
 | Number of correct productions                                    | 2 min                 |
| Note. HVLТ: Hopkins Verbal Learning Test; MEM-III: Wechsler Clinical Memory Scale - 3 ème edition; TMT: Trail Making Test |                                                                                                                                  |                                                                  | Total :
1h |

All the neuropsychological tests will be offered in two sessions (30 min each), between which a 20-min questionnaire session and the removal of the PSG (45 min) will take place, at each time of the study and in the same chronology (*Figure 6*).

[figure not shown]

**Figure 6.** Cognitive battery timeline

Note. MEM-III: Wechsler Clinical Memory Scale - 3ème edition; HVLТ: Hopkins Verbal Learning Test; TMT: Trail Making Test

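### The cortisol awakening response is timed by a self-written collection time that is not tied to waking, and the bedtime sample is assigned to the research unit while the night is spent elsewhere

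*Protocol*

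**What the plan says.** Table 3 in section 9.1.4 schedules CAR samples at waking and 30 and 45 minutes later, and one bedtime sample, at each of T1, T2 and T3. For timing, participants receive "a table to enter the time of collection". On location, "Morning samples will be collected at the participant's home or hotel", to be kept cool and brought to the laboratory that morning. For all others, "The remaining samples will be collected in our research unit". The section lists factors to be collected because they may affect cortisol: age, body mass index, smoking, contraception and socio-educational status. Neither wake time nor sampling delay is among them.

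Section 8.4.2 spreads each assessment over two half-days, "separated by a night's sleep to allow polysomnography examination". For that night, section 8.6 says that "participants can either go home or stay in a hotel, at their own expense". Section 9.1.3 says of the polysomnography: "Recordings of brain activity (electroencephalography), eye movements, heart rate, respiratory rate and oxygen saturation will be made simultaneously throughout the night". Section 8.6 has technicians remove the equipment at the unit. Section 9.3.4 places this between the two cognitive sessions, where "a 20-min questionnaire session and the removal of the PSG (45 min) will take place".

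CAR serves hypothesis 5b of Axis 1 (section 6): "Sleep disturbances are also associated with hyperactivity of physiological stress systems". Table 2 also names it for Axis 2 objective 1c, the effect of stimulation on the stress systems.

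**The concern.** CAR is defined relative to awakening. A clock time of collection, with no wake time beside it, does not show where on the curve a sample lies. If a woman has been awake for some minutes before her first sample, that sample is already on the rising part of the curve.

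In most studies this would only add noise. Here disturbed sleep is the exposure and CAR the outcome of objective 5b. Should the delay grow with poor sleep, the error is tied to the exposure and more data will not average it out. The same applies to Axis 2 objective 1c if stimulation changes waking. Table 3 has no MRI samples at T3, so CAR is the only measure named for 1c that exists after stimulation.

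The bedtime sample is a separate problem of location. Followed literally, the instruction has it taken at the unit before the woman leaves for the night, so it would not be a bedtime value. Section 7.1 names the cortisol rhythm under the Axis 2 main criterion, and this sample is its evening end.

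**Working it through.** **Step 1. The plan's own count.** Table 3 at T1 and T2: 2 (MRI) + 3 (CAR) + 1 (bedtime) + 2 (rest) = 8. At T3: 3 + 1 + 2 = 6. Both match the stated totals, so the bedtime sample is a distinct planned sample at every assessment.

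**Step 2. Is an awakening time available?** The evening half-day ends with the equipment fitted, the night is spent at home or in a hotel, and the equipment comes off at the unit the next day. The home-or-hotel wording and the transport that morning tie the CAR samples to that same night. A scored final awakening should therefore be obtainable. No section links it to the saliva times.

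**Step 3. Effect of a delay on one profile.** Assumed true values are 12, 18 and 17 nmol/L at 0, 30 and 45 minutes, linear in between. The slope is (18 − 12)/30 = 0.2 per minute up to 30 minutes and (17 − 18)/15 = −0.067 after. If the first sample is *d* minutes late and the second is timed 30 minutes from it:

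measured rise = (18 − *d*/15) − (12 + 0.2*d*)

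- *d* = 0: 18 − 12 = 6.0
- *d* = 5: 17.67 − 13 = 4.67 (22% lost)
- *d* = 10: 17.33 − 14 = 3.33 (44% lost)
- *d* = 15: 17 − 15 = 2.0 (67% lost)

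The waking value meanwhile goes up, from 12 to 13, 14 and 15.

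**Step 4. Effect on the sleep–CAR association.** This was a simulation of 2000 runs per scenario with 75 women and no true link, using a Pearson test at two-sided 0.05. All inputs except the 75 are assumed: waking cortisol mean 10, SD 3; rise mean 7, SD 4; peak at 32 minutes; assay SD 1; random delay SD 5 minutes. The increase score is the mean of the second and third samples minus the first. Ranges cover two patterns: the whole series late, or only the first sample late.

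| Extra delay per SD of poorer sleep (mean delay) | Increase score: r; false positives | Waking level: r; false positives | Total area: r; false positives |
|---|---|---|---|
| 2.5 min (5 min) | −0.18 to −0.19; 34–38% | +0.17 to +0.18; 31–34% | +0.05; 6–7% |
| 5 min (10 min) | −0.40 to −0.43; 95–98% | +0.30; 76% | +0.08 to +0.09; 11–13% |
| 10 min (15 min) | −0.59 to −0.66; 100% | +0.41; 96–97% | +0.09 to +0.14; 12–22% |

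With no delay, or a mean delay of 10 minutes unrelated to sleep, the false-positive rate is 4–6% for all three measures.

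**Step 5. The bedtime sample.** Table 3 requires a bedtime sample. Section 9.1.4 exempts only morning samples from collection at the unit. Sections 8.6 and 9.1.3 have the woman sleep at home or in a hotel. These three statements cannot all be followed.

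**The case against.** Choosing how CAR is computed is usually left to a statistical analysis plan, and nothing here forbids using polysomnography times later. That is true of the analysis. It does not cover what participants are told to write down and where samples are taken, which are collection instructions. An analysis plan cannot turn a sample taken at the unit into a bedtime value.

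A reader might infer that the collection table is the only source of timing, or that polysomnography certainly captures waking before every CAR. Neither is supported. An actigraph and sleep diary are issued for the two weeks before each assessment (sections 8.4.4, 8.4.5 and 9.1.2). The recording is described as covering the night, without saying that it still runs at waking. That CAR falls on that morning is also an inference, though a strong one. The visit schedules in Figures 2 and 3 are not visible, so sampling times shown there cannot be excluded.

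It can also be said that the bedtime instruction is loose wording meant for the MRI and rest samples. That is plausible, but the sentence as written still needs correcting.

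Lastly, CAR is a secondary measure in a study that section 12.1 calls exploratory. That limits the consequence but does not remove the gap.

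**Conclusion.** The point holds in conditional form. The protocol does not tie CAR sampling to waking, and if delay grows with poor sleep the sleep–CAR association can be biased. A reader might go further and conclude that the plan does create a false link. The documents do not show that poor sleepers sample late, and a delay unrelated to sleep leaves the error rate at about 5%. Every size above rests on an assumed cortisol curve and assumed delays.

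Nor can one direction be claimed. The protocol's measure is cortisol levels, with no CAR index defined. A late start lowers an increase score, which works against hypothesis 5b, raises the waking level, and changes total area little.

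The bedtime instruction contradicts Table 3 and section 8.6 as written. It might be inferred that an early sample would manufacture the flatter rhythm predicted for patients. It would not by itself, because all groups follow the same procedure.

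The change should be made: the objectives affected are mostly secondary, but the bias would depend on the exposure and the remedy is nearly free.

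**What to change.** - In section 9.1.4, add wake time to the collection table beside each morning's sampling times.
- Derive minutes since the final awakening from that night's scored polysomnography. Use the diary or actigraph as back-up where the recording does not cover waking.
- In section 12.2, state that the CAR analyses use actual minutes since awakening.
- Exclude mornings with a late first sample only as a sensitivity analysis, with the limit fixed in advance (for example 10 or 15 minutes). Note that this may remove poor sleepers selectively, so it should not be the main analysis.
- Reconcile sections 8.6 and 9.1.4 so that the bedtime sample is taken at home or hotel at bedtime, and say how it is stored until morning.

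The cost is one column in a form, one variable derived from a recording that is scored anyway, and some profiles set aside in the sensitivity analysis. How many cannot be told from the protocol.

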## 9.2 Functional connectivity and cortical structures

aMRI and fMRI examinations will be offered on the same day at T1 and T2 of the study. The complete procedure will be explained to participants before they set up. Anatomical volumes will be acquired first, followed by fMRI sequences (activation and resting task). An off-camera debriefing questionnaire (10 min) will then be administered. A video recording will be made of the participants' faces, to check that they have not slept during the resting fMRI session. Similarly, physiological measurements will be taken during the MRI examination to enable adequate pre-processing of the data, as physiological parameters are known to have an impact on the BOLD signal. To this end, a physiological signal recording system (BioPac) will be used to jointly measure respiration and pulse wave or plethysmography (oxygen saturation of the blood) with the same box. Respiration will be measured using a strap placed over the chest. The pulse wave is measured with an oximeter placed on the index finger.

aMRI and fMRI examinations will be carried out on the 3T GE Premier imager in the Cyceron site. The GIP CYCERON holds an authorization for research involving the human person for studies in physiology and physiopathology in humans using nuclear medicine and magnetic

resonance imaging techniques. This authorization to carry out MRI studies was issued by the ARS on September 22, 2020 for a period of 3 years.

The measures selected are presented in Table 4.

**Table 4** MRI measurements

| MRI sequences            | Test                  | Usefulness/measures taken                                               | Duration ≈           |
|--------------------------|-----------------------|-------------------------------------------------------------------------|----------------------|
| Anatomical (aMRI) | T1 3D                 | Functional data pre-processing
Cortical surface                      | 6 min                |
|                          | T2 Flair              | DTI data pre-processing
White matter lesions                         | 6 min                |
|                          | DTI                   | White matter microstructure                                             | 8 min                |
| Functional (fMRI) | Rest task             | Rumination
Activation control
Functional connectivity             | 12 min               |
|                          | Activation task (ANT) | Attentional performance
Cognitive control
Functional connectivity | 20 min               |
|                          |                       |                                                                         | Total: 52 min |

**Note.** DTI: Diffusion Tensor Imaging; ANT: Attentional Networks Test

